### Sample size

As a feasibility study, there is no formal power calculation based on clinical non-inferiority for a diagnostic intervention [17]. To ‘quantify’ and assess the concept that imaging-based surveillance is not inferior to clinical slit-lamp examination in the detection of active anterior uveitis in children at risk, the starting point will be that that SLE findings (assumed to be abnormal in 100% of children with an active anterior uveitis) and AS-OCT findings will concord in at least 95%.

### Recruitment

Following identification through medical record review and confirmation of eligibility at routine clinical review, participants and their families will be approached postally, using posted participant information sheets, or by telephone, 1-2 weeks prior to the next planned outpatient attendance. Informed consent will be sought from parents of participants by a member of the research team within a week of being given the study documentation. Assent will also be sought from participating children where appropriate [18,19] (see supplemental material 3 (S3) for the consent and assent forms to be used in the study). To minimise participant attrition, after entering the trial families will receive telephone calls a few days ahead of each visit to support attendance, and financial support for travel costs.

### Randomisation and allocation

Coordinated registration and allocation of participant trial numbers will be used. Participants will be allocated using computer-generated permuted block randomisation into one of two arms (1:1, block size = 4) stratified by age (8 and under, over 8). This will be undertaken centrally by the coordinating trial team using Sealed envelope (www.sealedenvelope.com). Allocation will not be concealed, and participants cannot be masked to their allocation to routine (slit lamp examination) or imaging-based surveillance (AS-OCT) examinations.

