## Abstract

Children with Juvenile Idiopathic Arthritis (JIA) are at a currently unpredictable risk of a blinding, often asymptomatic, co-existent eye disorder, anterior uveitis which requires prompt treatment. The unpredictability of this insidious disorder commits children with JIA to three-monthly expert clinical examinations in specialist eye centres often located far from their homes. Optical coherence tomography of the ocular anterior segment (AS-OCT) has been shown to be an acceptable, repeatable and sensitive modality for uveitis detection, but is not standard care. This feasibility randomised controlled trial (RCT) aims to inform a future full-scale RCT comparing current routine practice (expert slit lamp examination, SLE) to AS-OCT for the surveillance of uveitis in children at risk. Eighty children aged between 2 and 12 years old and diagnosed with JIA within the preceding year will be included. Participants with an existing diagnosis of uveitis, other ocular co-morbidities or those unable to complete examinations or provide informed assent will be excluded. Participants will be randomised to SLE (control) or AS-OCT (intervention) examination at a frequency consistent with the current national programme for childhood uveitis surveillance. Children in the intervention arm will also have standard examination at 6 and 12 months after study entrance. Outcomes of interest will be feasibility (recruitment and attrition rates), clinical metrics (proportion diagnosed with uveitis or other ocular disorders at 12 months after study entrance), quality of life outcomes (PedsQL), and resource use. Additionally, comparative analysis of AS-OCT versus SLE (‘gold standard’ reference testing) findings at 6 and 12 months for those in the intervention arm will provide the proof-of-concept data necessary to develop and undertake a larger scale trial. Trial registration: This trial has been registered with clinicaltrails.gov (NCT05984758).

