### Study design

This study will be a two-arm, parallel group, single site feasibility randomised controlled trial (RCT) comparing slit lamp examination-based (SLE, routine care) with AS-OCT based detection of active anterior chamber inflammation over 52 weeks in children undergoing surveillance examinations for juvenile idiopathic associated uveitis. Study participants will be children newly diagnosed (within the preceding 12 months) with JIA. The primary outcomes will be study feasibility metrics (i.e., recruitment and attrition rates). Proof of concept analyses will also be undertaken, with comparison of AS-OCT assessment to ‘gold standard’ clinical examination at 6 and 12 months.

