There are limitations inherent in the design of the proposed study. Firstly, due to the study design, it is not possible for the participants and research team to be masked to the arm to which participants have been allocated, and this may introduce the risk of researcher bias. Equally, due to the nature of the intervention, it is not possible for study participants to be masked to their study arm, which also potentially risks information bias in patient reported outcomes. A pragmatic design, in which each child undertook both standard and interventional examination, with randomisation of which examination would be used for assessment, may be the approach taken for future studies, informed by the findings of this feasibility trial. Secondly, recruitment will only take place at a single site, potentially limiting the generalisability of the data. Additionally, this site is a highly specialised care setting, with participants poorly representative of the ‘average’ patient. Again, as this is a feasibility study, informing a future larger scale study, there will be exploration and description of the representativeness of the recruited patient sample, and reflection of how that compares to what is known about the characteristics of the wider population of children at risk. Participants in this study will be reimbursed for their travel and will consent to regular phone calls to support attendance. As this deviates from routine care, it can be argued that this reduces the generalisability of the study. However, the findings from this study will provide a baseline for best achievable attrition rate to as comparison for the full RCT, where generalisability will be considered again.

In conclusion, this study will provide vital information about the feasibility of conducting a larger scale trial on SLE versus AS-OCT uveitis screening examinations for children with JIA. The data collected in this study will also provide valuable insight into the practical considerations needed before implementing this into a larger scale RCT.

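### The plan says allocation will not be concealed and publishes a fixed block of 4 at one open site, so up to a third of assignments could be foreseen

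*Protocol article*

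**What the plan says.** The section Randomisation and allocation in the protocol article specifies "computer-generated permuted block randomisation into one of two arms (1:1, block size = 4"), "stratified by age (8 and under, over 8"). On who does it: "This will be undertaken centrally by the coordinating trial team using Sealed envelope". The next sentence reads "Allocation will not be concealed, and participants cannot be masked to their allocation".

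Three other places bear on the point:

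- Study design describes a "two-arm, parallel group, single site feasibility randomised controlled trial (RCT").
- Recruitment says "Informed consent will be sought from parents of participants by a member of the research team".
- The Discussion gives as a limitation that "it is not possible for the participants and research team to be masked to the arm to which participants have been allocated".

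The Discussion treats the lack of masking as a limitation. It neither mentions nor justifies a lack of concealment.

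**The concern.** Concealment and masking protect against different things. Concealment acts before assignment: whoever decides whether and when to enrol a child does not know which arm comes next. Masking acts after assignment. That a slit lamp examination cannot be disguised as a scan rules out masking the participant, but it has no bearing on concealment. One sentence in the plan treats the two together and says the first will not be done.

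If the arm is known or can be worked out in advance, enrolment can be influenced without bad faith. A recruiter may hesitate over a restless child when the next place is imaging, or may read the exclusion for difficulty in cooperating with examination more strictly. The arms may then differ at entry for reasons other than chance, and no later analysis reliably repairs that.

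The parts of the plan most exposed are:

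- the chi-square comparison of the arms in the Analysis section, which also counts missing outcomes as adverse;
- PedsQL, and adherence and attrition where they are looked at by arm;
- the progression criterion on sight-threatening complications, which is measured in the imaging arm only and so depends on which children enter it;
- possibly the proportion of eligible patients recruited, since a refusal or delay at the point of approach enters that figure.

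**Working it through.** The plan gives no figure for predictability, so there is nothing of its own to reproduce. The check asks how much a recruiter could deduce if the sentence means only that the trial is open-label.

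**Inputs**

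- 1:1 ratio, fixed block of 4, two age strata (Randomisation and allocation).
- One site (Study design), with past assignments visible to the research team (Discussion).
- 80 children: "Eighty children aged between 2 and 12 years old" (Abstract).
- Assumption: the recruiter tracks every past allocation in each stratum and knows where blocks begin.

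**One block of 4.** There are 6 equally likely sequences of two A and two B. An assignment is certain when one arm is used up within the block. The best guess is the arm with more places left, or a coin toss when they are equal.

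| Place in block | Probability that it is certain | Probability that the best guess is right |
|---|---|---|
| 1st | 0 | 0.500 |
| 2nd | 0 | 0.667 |
| 3rd | 1/3 | 1/3 × 1 + 2/3 × 0.5 = 0.667 |
| 4th | 1 | 1.000 |
| Sum | 1.333 | 2.833 |

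- Certain: 1.333 / 4 = 33.3%. Counted over all sequences, this is 8 of 24 places.
- Guessed correctly: 2.833 / 4 = 70.8%.

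**Scaled to 80 children**

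- Certain: 80 × 0.333 = 26.7, about 27.
- Guessed correctly: 80 × 0.708 = 56.7, against 40 by chance.

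**Incomplete last blocks.** The article gives no expected age split, so a range was simulated. From 40/40 to 61/19 children per stratum, certain assignments run from 25.3 to 26.7 and correct guesses from 56.2 to 56.7. The result hardly depends on the split.

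**Effect of varying the block size.** Sizes drawn at random were simulated for two strata of 40 (an illustrative assumption), with a guesser who knows the set of sizes but not the block boundaries.

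| Block sizes | Certain, per 40 | Certain, of 80 | Guessed correctly |
|---|---|---|---|
| Fixed 4 | 13.3 | 27 (33%) | 70.8% |
| 2, 4, 6 | 1.62 | 3.2 (4.0%) | 27.97 / 40 = 69.9% |
| 4, 6, 8 | 0.95 | 1.9 (2.4%) | 27.03 / 40 = 67.6% |

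Varying the sizes removes nearly all the certainty but little of the guessing advantage. Keeping the sequence and the block sizes from recruiters is therefore the part that matters most.

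**The case against.** The strongest reply is that the sentence is only loose wording. Allocation is computer-generated and done centrally, and the same sentence goes on to speak of masking, so not concealed may well mean open-label. The article does not say that those who run the randomisation also seek consent. This reply carries weight. A reader might infer from the literal wording that the list is visible and all 80 assignments are known in advance, but no part of the document says so and that figure should not be used. The reply does not remove the point: on this reading the sentence still misstates a basic safeguard, and the fixed block of 4 remains.

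Second, the feasibility aims limit the damage. The main outcomes are recruitment, eligibility and attrition. The primary clinical outcome compares AS-OCT with slit lamp findings in the same children, so an imbalance between arms cannot bias it by setting unlike groups against each other. At most, steering changes which children are in that arm. This stands, and it lowers the severity.

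Third, steering is harder than the arithmetic suggests. Families are contacted one to two weeks ahead of a clinic visit and several may be in process together, so a child's place in the block is often unknown at first contact. Age is partly balanced by stratification, and reasons for exclusion are reported. This also stands in part: it makes 33% and 71% upper limits. It does not prevent discouragement at the point of consent.

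**Conclusion.** The point holds as one that should be fixed, not as one that undermines the trial. The sentence on concealment is wrong on either reading. If literal, it gives up a safeguard that the absence of masking does not require giving up. If it means open-label, it confuses two safeguards, and the fixed published block at one open site still lets a recruiter who tracks both strata know up to about one third of assignments (about 27 of 80) and guess about 71%.

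These figures measure predictability. They do not measure bias in any outcome, and neither its direction nor its size can be derived from the document. A reader might also infer that enrolment will be steered, or that the agreement result is compromised. The document supports neither: steering is a risk, and agreement is assessed within one arm. The risk lies mainly with the between-arm comparisons and the imaging-arm safety criterion, and the same habits could carry over to the full-scale trial that this study is meant to inform.

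**What to change.** Replace the sentence on concealment with wording such as: *The next allocation is concealed from staff who recruit. The central system releases it only after consent, eligibility and baseline data have been registered. Participants and the research team are aware of the arm once it has been allocated.* Open-label status is then described separately from concealment.

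For the allocations that remain, use randomly varying block sizes within the age strata, for example 4, 6 and 8, and do not disclose them to recruiting staff. Say plainly that this is a supplement: it removes most certain assignments but lowers guess accuracy only from 70.8% to about 67.6%.

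The cost is a change of wording, a change to the randomisation set-up and slightly looser balance within strata. The article does not describe how the randomisation service is configured, so the team should confirm that it can hold back each assignment until registration is complete. If recruitment has started, record the date of the change and the number of children already allocated.

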### Data collection and processing

Data will be entered into electronic data collection forms (DCFs) using the REDCap platform, with collection undertaken during study visits by research associates or clinicians and reviewed for completeness by an investigator. Alongside the data collection forms, optical coherence tomography (OCT) images will be collected from participants.

To limit data missingness, the following approaches will be used

- Validation rules within the REDCap form (i.e., form submission will not be permitted if data entry points have not been completed)

- Incoming data review monthly by the study team and screening committee to identify missingness, and any patterns of/ reasons for missingness within the study dataset

- Exclusion from outcomes analysis of participants lacking a full dataset for more than two consecutive study visits

Patient data will not be transferred to any party not identified in this protocol and will not to be processed and/or transferred other than in accordance with the patients’ (parent’s) consent. Direct access to the data will be granted to authorised representatives from the Sponsor, host institution and the regulatory authorities to permit study-related monitoring, audits and inspections. This trial will collect personal data (e.g., participant names), including special category personal data (e.g., participant medical information) and this will be handled in accordance with all applicable data protection legislation. Data (including special category) will only be collected, used and stored if necessary for the trial. The database and randomisation system will be designed to protect patient information in line with the GDPR. All documents will be stored securely and only accessible by study staff and authorised personnel.

### Analysis

Proportions will be reported as point estimates with 95% confidence intervals. Levels of missing data will be explored with respect to certain baseline characteristics, e.g., age and measures of disease severity to assess biases. All harms or unintended effects in each group will be reported. Initial trial success will be defined as: recruitment rates of > 4 recruits/month, or generation of information on barriers to recruitment; adverse event (incidence of new sight threatening complications in imaging-based surveillance group) rate of 0; adherence to surveillance programme of > 75% or understanding of barriers to adherence. We will seek to identify potential cost drivers to inform the collection of the data for cost-effectiveness analyses within a future definitive study. Within this feasibility trial, effect sizes (of ‘discrimination’ of disease) and variability in outcomes will be estimated with 95% confidence intervals to inform the sample size calculations for a full-scale trial. Efficacy and safety will be analysed according to randomisation group set, which will include all patients who underwent randomisation and who had recorded outcomes (positive detection) during the first 12 months or who completed at least 12 months of surveillance examinations. Missing outcomes (due to attrition) will be considered as an adverse outcome. We will compare the two study arms groups using two-by-two chi-square tests for equality of proportions for disease detection/ adverse outcomes within the OCT arm as compared with the ‘gold standard’ slit lamp examination group.

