### Study intervention *-* AS-OCT

Children randomised to the intervention arm will undergo AS-OCT imaging to detect anterior chamber inflammation. The AS-OCT images will be acquired using the Optovue RTVue OCT (8 cross-sectional scans) and the Heidelberg Spectralis OCT2 machines (anterior segment cube scan). Images will undergo manual analysis by a trained clinician to identify the presence of inflammatory cells within the anterior chamber. A later semi-automated re-analysis of acquired images will be undertaken within one week of the examination using published protocols [12,14]. Full details of image acquisition and analysis processes are available in supplemental document 1 (S1).

Imaging will be undertaken at a frequency consistent with line with national guidance (Table 1) [9]. This comprises 6 study visits in total (at Month 2 following the first visit to establish eligibility, Month 4, Month 6, Month 9, and Month 12- see Table 1 for further details). The full participant schedule of assessments is shown in Fig 1, with specific details of the study procedures shown in Fig 2.

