**Fig 2 pone.0316410.g002:**
[figure not shown]
Details about the specific procedures during the intervention and control arm. * - See supplemental document 2 (S2) for specific visual acuity screening protocol.

Exit from the study will occur either at visit 7 (for participants with a new diagnosis of JIA within 6 months of entrance to study), at visit 6 (for participants whose JIA was diagnosed within 6 to 12 months of study entrance, Fig 1), or at any visit where uveitis has been diagnosed. A diagnosis of uveitis will be made clinically, using slit lamp examination. Any child within the intervention arm in whom a ‘disease positive’ AS-OCT is acquired (i.e., more than 1 hyper-reflective particle in any cross-sectional scan) will undergo a confirmatory slit lamp examination. Confirmation of uveitis will lead to a child exiting the study.

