### Study outcome measures

The main outcomes of interest are the study feasibility metrics, specifically

- The proportion of patients within the service who meet the eligibility criteria, and reasons for exclusion

- The proportion of eligible patients recruited

- The proportion of patients who withdraw due to loss of consent or are lost to follow-up

- Statistical parameters (point estimates and range/ variance) of the clinical and patient centred outcome measures

The primary clinical outcome measured (as a surrogate endpoint) will be:

- Agreement, for participants in the intervention arm, of AS-OCT findings with routine clinical examination, analysed at 6 months and 12 months milestones

Other clinical outcomes of interest will be:

- New diagnosis of uveitis

- New diagnosis of other visual/ocular problems

We shall be evaluating patient centred outcomes, specifically

- Health related quality of life (PedsQL child self-report, at 12 months and change from

baseline to 12 months)

We shall also be evaluating resource use across the feasibility study to support the design of cost-effectiveness analyses in the larger scale study.

Adverse and serious adverse events (AE/SAE) will be recorded for both the intervention and routine care arms. These events comprise (1) Development of anterior chamber inflammation; (2) development of non-sight threatening sequalae of ocular inflammation during the study period; (3) progression or disease flare of JIA; (4) development of treatment related adverse events. AE/SAE occurring in the intervention arms will be used as criteria to determine progression to a full RCT. Specifically. the progression criteria will be defined using a ‘traffic-light’ system (green – criteria met, amber – minor changes needed, red – significant changes needed).

Recruitment

-Green – > 4 recruits/month-Yellow – 2-4 recruits/month-Red – < 2 recruits/month

Adverse events (incidence of sight threatening complications in imaging-based surveillance group)

-Green/ Yellow – No cases-Red – > 1 case

Adherence to surveillance programme

-Green – > 75%-Yellow – 30-75%-Red – < 30%

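### The recruitment and adherence parts of initial trial success can each be met by an alternative with no threshold, so they cannot realistically fail, and the article does not relate this rule to its traffic-light progression criteria

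*Protocol article*

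**What the plan says.** The protocol article contains two decision rules.

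**Success rule (Analysis).** Initial trial success has three components:
- recruitment: "recruitment rates of > 4 recruits/month, or generation of information on barriers to recruitment"
- adverse events: "adverse event (incidence of new sight threatening complications in imaging-based surveillance group) rate of 0"
- adherence: "adherence to surveillance programme of > 75% or understanding of barriers to adherence"

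The recruitment and adherence components each offer an alternative to the number. The adverse-event component does not.

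**Progression rule (Study outcome measures).** For the move to a full trial, "the progression criteria will be defined using a ‘traffic-light’ system (green – criteria met, amber – minor changes needed, red – significant changes needed". For recruitment, green is above 4 per month and the lower bands are "2-4 recruits/month-Red – < 2 recruits/month". For adherence, green is above 75%, yellow is 30% to 75% and red is below 30%.

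**Visit counts (minor).** The section on the AS-OCT intervention says "This comprises 6 study visits in total". The Fig 1 legend lists 6 visits for children within 6 months of diagnosis and 5 for later entrants. The text below Fig 2 says "Exit from the study will occur either at visit 7" for the first group and at visit 6 for the second.

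**The concern.** The Study design section names recruitment and attrition as the primary outcomes, and the trial exists to inform a full-scale RCT. A criterion is useful for that purpose only if some plausible result would fail it.

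The alternatives in the success rule set no amount or standard of information. They also work in the wrong direction: the worse recruitment or adherence is, the more there is to learn about barriers, and the more easily the alternative is met. Whether enough was understood would then be judged with the results in view.

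The two rules share their upper cut-offs (above 4 per month, above 75%), so without the alternatives they would agree on what counts as fully met for recruitment and adherence. With them, a result in the yellow or red band can also be reported as meeting the success component. The article does not tell the reader which statement to act on.

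**Working it through.** The plan states no power, error rate or probability for the success rule, so there is no figure to reproduce. The check is a comparison of the two rules, followed by an illustration.

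**1. The rules side by side**

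| Result | Traffic light | Success component |
|---|---|---|
| > 4 recruits/month | green | met on the number |
| 2-4 recruits/month | yellow | met if barrier information is generated |
| < 2 recruits/month | red | met if barrier information is generated |
| adherence > 75% | green | met on the number |
| adherence 30-75% | yellow | met if barriers are understood |
| adherence < 30% | red | met if barriers are understood |

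**2. Will the alternative be met?** Study outcome measures lists, as planned outputs, the eligible proportion with reasons for exclusion, the proportion of eligible patients recruited, and the proportion who withdraw or are lost. The Discussion adds interviews with 10 participants on acceptability. All of these are planned irrespective of the rates achieved. With no threshold set, they will almost certainly supply some information on barriers.

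**3. Illustration.** Assumptions, none of them from the article:
- Recruits in T months follow a Poisson distribution with mean λT. T = 20, because 80 children at 4 per month take 80/4 = 20 months.
- Adherence is a proportion of n = 80 children. Above 75% means at least 61, because 60/80 is exactly 75%.
- Each alternative is met with chance q, independently of the rest.

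Formulas:
- Number alone, recruitment: P_R = P(X > 80), X ~ Poisson(20λ)
- Number alone, adherence: P_A = P(Y ≥ 61), Y ~ Binomial(80, p)
- With the alternatives, both met: [1 − (1 − P_R)(1 − q)] × [1 − (1 − P_A)(1 − q)]

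| True state | Both met, numbers alone | q = 0.90 | q = 0.95 | q = 1 |
|---|---|---|---|---|
| 1/month, 20% (red on both) | about 0 | 0.81 | 0.90 | 1.00 |
| 3/month, 50% (yellow on both) | about 8 × 10⁻⁹ | 0.81 | 0.90 | 1.00 |

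In the first row P_R and P_A are about 0, so the result is simply q²: 0.90² = 0.81 and 0.95² = 0.9025.

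**4. After deleting the alternatives** the numeric criteria discriminate:

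| True recruits/month | 1 | 2 | 3 | 4 | 5 |
|---|---|---|---|---|---|
| P_R, T = 20 | about 0 | about 0 | 0.006 | 0.47 | 0.98 |
| P(X > 4T), T = 30 | about 0 | about 0 | 0.001 | 0.48 | 0.99 |

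| True adherence | 20% | 50% | 70% | 75% | 80% |
|---|---|---|---|---|---|
| P_A, n = 80 | about 0 | about 0 | 0.14 | 0.46 | 0.84 |

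T = 30 is included because the approved protocol version is dated October 2023 and recruitment is expected to end by April 2026, about 30 months at most. The choice of T does not change the picture.

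**5. Visit counts**

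| Place | Entry within 6 months of diagnosis | Later entry |
|---|---|---|
| AS-OCT intervention section | 6 (first visit plus Months 2, 4, 6, 9, 12) | not given separately |
| Fig 1 legend | 6 (Day 1, Weeks 8, 16, 28, 40, 52) | 5 (Day 1, Weeks 13, 26, 39, 52) |
| Text below Fig 2, exit visit | 7 | 6 |

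The first two places agree. The third is one higher in both groups.

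**The case against.** The strongest defence is that the two rules answer different questions. One sets progression to a full trial and the other sets the success of this feasibility study. Learning why families decline or miss visits is a legitimate aim, and the Introduction and Discussion both say the study is to inform recruitment and retention approaches. Red is defined as needing significant changes, not as failure, so a study could be red and still have learned what it set out to learn. The rates will be reported whichever rule is used, and participant safety and the estimates are unaffected.

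Much of this stands, and it rules out several stronger readings:
- **That the success rule can never fail.** It can. The adverse-event component requires a rate of 0 and has no alternative.
- **That the traffic lights are overridden, or that the two sections give opposite verdicts.** The article gives neither rule precedence, and the labels differ. What the text supports is that the relation between them is not stated.
- **That the two components are met with 100% probability.** This holds only if q = 1. No figure in the article fixes q.
- **That the visit numbering moves children across the 75% adherence line,** for example 5/6 = 83% against 5/7 = 71%. The extra number may be a separately numbered eligibility visit that every participant attends. It would then add one above and below: 5/6 becomes 6/7 = 86%, and for later entrants 4/5 = 80% becomes 5/6 = 83%. All of these stay above 75%. Nor does the article define adherence as visits attended over visits scheduled.

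What the defence does not answer is that two of three stated success components have no realistic failing result. An aim of learning about barriers can be met and reported without making it an alternative route to success.

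**Conclusion.** The point holds for the recruitment and adherence components. Each can be met by an alternative with no threshold, which the planned outputs will supply at almost any rate, so only the adverse-event component can realistically fail. A trial below 2 recruits/month and below 30% adherence would be red on both progression criteria and would still meet both success components. The article leaves the link between the two rules unstated.

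This conclusion is logical and rests on the wording and the list of planned outputs. The probabilities show scale only and depend on the assumed q, the Poisson and binomial models, independence, and adherence as a per-child proportion.

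The visit numbering is a separate, minor inconsistency with no demonstrated effect on the adherence criterion.

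**What to change.** 1. In Analysis, delete both alternatives, so that recruitment and adherence succeed only above 4 per month and above 75%. These then match the green bands in Study outcome measures.
2. State that the traffic lights alone govern progression to the full trial.
3. Report information on barriers descriptively, and use it to decide which changes an amber or red result needs.
4. Separately, reconcile the exit-visit numbers below Fig 2 with the AS-OCT intervention section and the Fig 1 legend, for example by saying whether an eligibility visit is counted.

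If the sponsor prefers to keep the alternatives, the least that is needed is a sentence saying that initial trial success does not replace the traffic-light decision.

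The change is wording only, with no effect on data collection or sample size. Its cost is that the trial can then formally miss its success criteria. It is best made before the results are known.
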